## Abstract

**Background:**

Returning to work after long-term sick leave can be challenging, particularly in small- and medium-sized enterprises (SMEs) where support may be limited. Recognizing the responsibilities and challenges of SME employers, a web-based intervention (hereafter the SME tool) has been developed. The SME tool aims to enhance the employer’s intention and ability to support the sick-listed employee. Based on the Self-Determination Theory, it is hypothesized that this intention is enhanced by intervening in the employer’s autonomy, competences, and relatedness targeted at, e.g., communication with sick-listed employee, involvement of other stakeholders, and practical support. This is achieved by means of providing templates, communication videos, and information on legislation. This article describes the design of an effect and process evaluation of the SME tool.

**Methods:**

A randomized controlled trial (RCT) with a 6-month follow-up will be conducted with a parallel-group design with two arms: an intervention group and a control group. Sick-listed employees (≤ 8 weeks) of SMEs (≤ 250 employees) at risk of long-term sick leave and their employers will be recruited and randomly allocated as a dyad (1:1). Employers randomized to the intervention group receive unlimited access to the SME tool, while those in the control group will receive care as usual. The primary outcome is the satisfaction of the employee with the return to work (RTW) support provided by their employer. Secondary outcomes include social support, work performance, and quality of work life at the employee level and self-efficacy in providing RTW support at the employer level. Outcomes will be assessed using questionnaires at baseline and 1, 3, and 6 months of follow-up. Process evaluation measures include, e.g., recruitment and use of and perceived usefulness of the SME tool. Additionally, semi-structured interviews with employers, employees, and occupational physicians will explore the interpretation of the RCT results and strategies for the national implementation of the SME tool.

**Discussion:**

The SME tool is hypothesized to be valuable in addition to usual care helping employers to effectively support the RTW of their long-term sick-listed employees, by improving the employers’ intention and ability to support.

**Trial registration:**

ClinicalTrials.gov, NCT06330415. Registered on February 14, 2024.

**Supplementary Information:**

The online version contains supplementary material available at 10.1186/s13063-024-08383-4.

## Introduction

Employees working in small- and medium-sized enterprises (SMEs) represent the majority of the workforce and, as such, contribute significantly to the global economy [1]. To illustrate, SMEs comprised 99% of all enterprises in the European Union and employed 66% of all employees in 2020 [1]. Although lower rates of sick leave occur in SMEs, compared to larger organizations, they are also more vulnerable to the consequences of such absence [2–6].

Compared to larger organizations, owners of smaller enterprises face limitations in financial and practical resources, and they often lack the expertise to support employees’ return to work (RTW) [6]. Resources and expertise include human resources, formal procedures, extended income payments, and access to specialized expertise in managing workplace accommodations or employee support [6–8]. Employers of smaller enterprises have expressed uncertainty regarding their engagement with involved parties and regarding legislation during the RTW [9]. They often have many different responsibilities besides addressing RTW matters, certainly after extended periods of workforce absence [4, 6, 10]. Although employers of SMEs generally maintain close relationships with their employees, time constraints and conflicting interests can reduce the provided RTW support and as a consequence the employee’s satisfaction with the received support [8, 11, 12].

To address the challenges faced by SME employers in supporting the RTW of employees, a web-based intervention (hereafter the SME tool) targeted at employers of SMEs has been developed [13]. As SMEs have been identified as hard to reach, web-based interventions are promising for employers of SMEs to provide convenient, accessible, and cost-effective resources [14]. The SME tool aims to improve the intention and ability of SME employers to provide appropriate support during sick leave and RTW, thereby enhancing the satisfaction of long-term sick-listed employees with the received support from their employer.

The SME tool is developed with the use of the Intervention Mapping (IM) approach, which follows a systematic six-step approach to intervention development [15], and focuses on changing the behavior of the target group, that is in our case, of employers. The desired behavioral change of employers in providing support is outlined in a logic model of change (see Additional file 1) and based on the Self-Determination Theory [16]. This behavioral change theory is chosen because it aligns with the specific characteristics of employers in SMEs. In order to improve the intention to express the behavior of supporting RTW, that is the intrinsic motivation of employers, three behavioral determinants are targeted. Firstly, the component *autonomy* relates to aligning actions with company norms and values, emphasizing independence and flexibility in decision-making, which is crucial in the dynamic nature of SMEs. This is for example reflected in wanting flexibility in when which stakeholder is involved. Secondly, the component *competence* involves the skills and knowledge necessary, for example, for providing practical RTW support. Lastly, the component *relatedness* aligns with the family-like structure often found in SMEs, for example fostering good communication [4, 8].

A randomized controlled trial (RCT) will allow an assessment of the contribution of the SME tool beyond usual care. Research examining employers and employees together within one study design is scarce, but the protocol presented in this study is based on and aligned with previous research and recommendations [17, 18]. By addressing the needs of SME employers, the SME tool could fill an important gap in usual care. Interventions targeting SME employers have, so far, not frequently been developed and evaluated, thus emphasizing the importance for a comprehensive process evaluation to be incorporated as well [19].

This paper describes the design of an RCT that aims to evaluate the effectiveness of the SME tool on the satisfaction of the employee with the RTW support provided by their employer, in comparison to a control group of employer–employee dyads receiving care as usual. The aim of the process evaluation is to clarify the results regarding the effectiveness, to improve the tool if needed, and to explore potential strategies for the national implementation of the SME tool, in case the intervention proves to be effective.

## Methods

### Design

The study will employ a two-arm RCT design with a 6-month follow-up and a process evaluation. The study will be conducted in the Netherlands. For details regarding the Dutch context, we refer to Table 1. Table 2 depicts the timeline from enrolment to measurement timing. The flowchart of the study design is shown in Fig. 1. The study compares employer–employee dyads randomized to the intervention group with employer–employee dyads randomized to the control group. The trial will use a parallel group design with an allocation ratio of 1:1 and follows a superiority framework. The Standard Protocol Items for Clinical Trials (SPIRIT) guidelines were used in the writing of this protocol (see Additional file 2) [20]. The study protocol has been reviewed by the Medical Ethical Review Committee (METC) of the Amsterdam University Medical Center (Amsterdam UMC), the Netherlands (METC2023.0880). The METC has exempted the study protocol from ethical review according to the Dutch Medical Research Involving Human Subjects Act (WMO). In addition to the trial registration (NCT06330415), all items of the World Health Organization Trial Registration Data Set are outlined in Additional file 3.

**Table 1 Tab1:** Occupational healthcare in the Netherlands

This study is conducted in the Netherlands, where the employer together with the sick-listed employee is responsible for the RTW during the first 2 years of sick leave [21, 22]. Employers are obligated to continue paying the employee’s salary during these first 2 years, though the specific percentage varies based on the collective labor agreement or employment contract [22]. The Gatekeeper Improvement Act outlines the shared responsibility of employers and employees during sick leave and RTW, emphasizing a structured RTW approach [17, 20]. In the Dutch occupational healthcare system the involvement of an occupational physician (OP) is mandatory in case of risk of long-term sick leave. OPs fulfill a consultative role, acting as key intermediaries between employers, employees and the healthcare system. Their expertise lies among others in translating employees’ medical restrictions into work-related constraints or work(place) adaptations that need to be addressed for RTW [22].

**Table 2 Tab2:**
[figure not shown]
A schedule of enrolment, intervention, and assessments

**Fig. 1 Fig1:**
[figure not shown]
A participant flowchart of the randomized controlled trial

### Participants

We aim to include 202 employer–employee dyads, thus a total of 404 participants. Both employees and employers will receive a voucher of 20 euros after participating in the study, i.e., when all questionnaires are completed. Employees at study enrolment should:Be of working age (18–65 years);Have a fixed or temporary employment contract at a SME (≤ 250 employees), with a minimum of 6 months remaining in their contract;Be currently sick-listed or partially sick-listed (≤ 8 weeks), with a risk of long-term absenteeism, based on the likelihood of the duration of sick leave exceeding 2 months as assessed by their occupational physician (OP, in plural OPs);Be able to understand and read Dutch sufficiently, in order to complete the questionnaires;Not have a colleague who is already participating in the study.

Subsequently, the employer of the participating employee will be included. At the time of study entry, the employer should be:An employer, supervisor, (case)manager, or HR manager of a SME (≤ 250 employees). In this study, the employer is appointed by the employee and refers to the person who is in direct contact with the employee, and thus the person who offers the RTW support to the employee;Able to understand and read Dutch sufficiently, in order to use the SME tool and complete the questionnaires.

### Recruitment

#### Involvement of OPs

Employees will be recruited via approximately 40 OPs. Upon the employee’s consent, the OP will invite the employee’s employer, so that dyads are formed, i.e., employer–employee dyads [18]. We anticipate the involvement of 10 occupational health services, along with multiple freelance OPs, aiming to enlist a total of 40 OPs. We aim to achieve a diversity in the size of occupational health services and the sectors they deliver their service to, with an emphasis on those servicing SMEs. In approaching OPs for the involvement in our study, we will host an informative meeting and use a video to explain the aim and methodology of the study. The executing researcher of the study (DB) provides the OPs with a detailed information package. Continuous communication will be maintained with OPs throughout the study, preceding the inclusion of the dyads and following randomization. OPs are free to recruit additional participants. The OPs will assist in the process but do not handle consent directly. The responsibility for recruiting participants and obtaining informed consent lies with the executing researcher (DB). The executing researcher (DB) and research assistant—under supervision of the principal investigator (FS)—will identify potential recruits and obtain informed consent.

#### Recruitment of employees

Employees will be recruited via OPs in the Netherlands from May 2024. These OPs will approach potential eligible employees during their usual sick leave consultation hours, with an invitation letter, information sheet, consent form, and return envelope. The employees will be asked to return this form to the executing researcher of the study (DB) if they are interested and willing to participate. The above steps can also be carried out digitally, according to the employees’ preferences. Thereafter, researcher DB will contact the employee by phone to explain the study, to check the employee’s eligibility according to the inclusion criteria, and to give the employee the opportunity to ask questions. If an employee is eligible and willing to participate, he or she can sign informed consent (see Additional file 4) and subsequently appoint his or her employer.

#### Recruitment of employers

Subsequently, the OP assesses the eligibility of the employer and will invite eligible employers via telephone or e-mail to participate. A digital informed consent form will be sent to the employer (see Additional file 4). The executing researcher (DB) offers the opportunity for contact and addressing questions. In case the employer is not interested in participation, the employee is unable to participate in the study, as only employer–employee dyads can participate. After signing the form, the dyads will be assigned a unique number in chronological order of inclusion, starting at 001. After inclusion, participants will be asked to complete the baseline questionnaire digitally and the dyads will thereafter be randomized to the intervention or the control group.

## Sample size calculation

The sample size calculation for this RCT is based on the primary outcome measure: the linear rate of change in the employees’ perceived satisfaction with their employer’s RTW support with respect to the satisfaction at baseline, over a period of 6 months after the beginning of the trial. Based on a prior study involving 3470 employees with various conditions, the expected mean score for the question on satisfaction at baseline is considered to be 2.64 (range 1–5) with a standard deviation of 1.05 [23]. Assuming a 20% improvement after 6 months in the intervention group and no relative improvement in the control group, it is anticipated that the intervention group will achieve a mean score of 3.17 resulting in a linear change rate of 0.53 over a period of 6 months. We estimate the effect of the SME tool on our primary outcome using a linear mixed model with a random intercept and slope for each OP to account for clustering due to OPs recruiting employer–employee dyads. In this model, we estimate the linear effect of the time, and the interaction between time and treatment on the primary outcome using the data collected at 3 and 6 months follow-up. The models are also adjusted for the satisfaction outcome value at the baseline. Assuming an intracluster correlation coefficient of 0.1, both the intervention and control arms need 80 employees to achieve 80% statistical power for detecting a significant difference in the change rate of 0.088 per month of the outcome over time between the intervention and control group at the significance level $$\alpha =0.05$$ [24]. In total, we plan to recruit 202 dyads, which equals 404 participants, to allow for an attrition rate of 20%. The sample size calculation was performed using nQuery [24].

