### Data collection

Self-reported questionnaires will be distributed digitally to employees and employers using the electronic data capture system Castor EDM [35], prior to randomization (baseline; T0), and after 1 (T1), 3 (T2), and 6 months of follow-up (T3). E-mail and phone reminders will be sent after 1 and 2 weeks, respectively. All data is securely saved in Castor EDC [35], processed in SPSS 25.0 [28], and stored on the secure sponsor’s surfer. The executing researcher (DB), principal investigator (FG), and project leaders (MG and ST) will be given access to the final data sets. No prior adverse events have been reported during digital employer interventions [17], and we do not anticipate any. However, should any adverse events occur, we will report them through the sponsor’s portal at the Amsterdam UMC.

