## Participant characteristics and effect measures

### Employees

At T0, the questionnaire contains questions about the personal and work-related characteristics of the employee (e.g., age, gender, reason for sick leave, educational level, work status, type of contract, type of work). Measures for effect evaluation will be assessed as change from baseline at each time point (i.e., T0, T1, T2, and T3), except for one time to event: *total number of sick leave days*. Table 3 depicts an overview of all outcome variables.

**Table 3 Tab3:** An overview of primary, secondary, and process outcome variables

Level	Construct	Measurement instrument; # items	Example item	Response categories	Score calculation
Primary outcome variable					
Employee	Satisfaction with the RTW support from employer	Questionnaire; Self-developed; 1 item	How satisfied are you with the sick leave and return to work guidance you have received from your employer since the sick leave/over the past month/3 months?	1) Very dissatisfied, 2) dissatisfied, 3) neutral, 4) satisfied, and 5) very satisfied	N/A
Secondary outcome variable					
Employee	Social support from employer	Questionnaire; Self-developed; 8 items	How important is it that your employer provides emotional support during sick leave and RTW? (importance); how much emotional support have you perceived form your employer? (amount of support)	1) Very unimportant, 2) unimportant, 3) neutral, 4) important, and 5) very important; 1) Very few, 2) few, 3) neutral, 4) much, and 5) very much	“Importance score” multiplied with “amount of support score” leads to “weighted score”, with higher scores indicating more social support from employer
	Total number of sick leave days	Questionnaire; Self-developed; 8 items	Have you worked in the past month/3 months? This can include both activities in your regular job as well as in adapted work	Yes or no options and open-ended responses to express current employment status, for example date input (e.g., return to work since:../../….)	The average number of working days per week divided by the contracted work days
	Work performance	Questionnaire; Maastricht Instrument for Sustainable Employability (MAISE), subscale 2A ‘work performance’; 6 items	I have the knowledge to perform my job well	1) Completely disagree, 2) disagree, 3) neutral, 4) agree, and 5) completely agree	Mean score, with higher scores indicating better work performance

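### The primary effect is defined as change from baseline over 6 months, but the tested interaction uses only 3- and 6-month scores and its anchoring is not stated; with a treatment main effect, power falls well below 80%

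*Protocol article*

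**What the plan says.** The protocol article's Sample size calculation section defines the primary outcome as the linear rate of change in satisfaction "with respect to the satisfaction at baseline, over a period of 6 months after the beginning of the trial". The baseline score is "considered to be 2.64 (range 1–5) with a standard deviation of 1.05". A 20% gain in the intervention arm and none in the control arm gives 0.53 points over 6 months, or 0.088 per month.

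The model is "a linear mixed model with a random intercept and slope for each OP to account for clustering" due to recruitment through occupational physicians (OPs). For the fixed part, it names a linear time effect and the "interaction between time and treatment on the primary outcome using the data collected at 3 and 6 months follow-up". Then: "The models are also adjusted for the satisfaction outcome value at the baseline". A treatment main effect is neither named nor excluded, and the time origin is not given.

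Two other sections bear on this. The Employees part of the effect measures says "Measures for effect evaluation will be assessed as change from baseline at each time point", listing T0 to T3. The Statistical analysis section gives longitudinal mixed models with random intercepts and slopes per OP, with no limit to particular visits and no list of fixed effects. Data collection schedules a questionnaire at 1 month as well as at 3 and 6 months.

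**The concern.** The quantity of interest starts at baseline, but the responses in the model start at month 3. Whether the interaction still measures change from baseline depends on one unstated choice.

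- **With a treatment main effect**, the arm difference at the time origin is estimated freely. With only two response times, the interaction is then the change in the arm difference between months 3 and 6. Any benefit already present at month 3 goes into the main effect, which is not the tested term.
- **Without a main effect, and with time counted from baseline**, the arms are held equal at month 0. The interaction is then a slope anchored at baseline.

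The choice matters because early benefit is plausible. Employers receive the tool after randomization, with reminders at 1 and 3 months. Under an early benefit that is maintained, the two fits of the same sentence give nearly opposite results. In an open-label trial that choice should not remain open once outcomes can be seen by arm.

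**Working it through.** **Inputs from the protocol.** Difference 0.53 at 6 months; SD 1.05 (variance 1.1025); 80 per arm; 80% power; alpha 0.05, taken as two-sided; ICC 0.1; about 40 OPs; 20% attrition. **Assumed, because not given:** exchangeable within-person correlation ρ, shown from 0.1 to 0.7.

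**1. Reproducing the plan's figure.** n per arm = 2 × 1.1025 × (1.960 + 0.842)² / 0.53² = 2 × 1.1025 × 7.849 / 0.2809 = 61.6. With 160/40 = 4 analysed dyads per OP (derived, not stated), the design effect is 1 + (4 − 1) × 0.1 = 1.3, and 61.6 × 1.3 = 80.1. Attrition: 80.1/0.8 = 100.1, so 101 per arm and 202 in total. Both stated figures are thus reproduced by a plain between-arm difference of 0.53 at 6 months.

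**2. Treatment main effect fitted.** Under linear growth the arm difference is 0.265 at month 3 and 0.53 at month 6, so the tested divergence is 0.265 over 3 months. Its standard error is √(4(1 − ρ) × 1.1025/80). The baseline covariate does not help, because it cancels from the within-person 3-to-6-month difference. Power is Φ(0.265/SE − 1.96).

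| ρ | SE | Power at 80 per arm | n per arm for 80% |
|---|---|---|---|
| 0.1 | 0.223 | 22% | 444 |
| 0.3 | 0.196 | 27% | 346 |
| 0.5 | 0.166 | 36% | 247 |
| 0.7 | 0.129 | 54% | 148 |

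Reaching 80% with 80 per arm needs ρ = 1 − 80 × 0.265²/(4 × 1.1025 × 7.849) = 0.84. If the difference is 0.40 at month 3 and 0.53 at month 6, the divergence is 0.13 and power is 8-17%. If the full 0.53 is present at month 3 and held, the divergence is zero. Simulation (160 employees, 40 OPs, ICC 0.1, ρ 0.3-0.7, 2,000 runs each) then rejected in 4.9-5.9% of trials.

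**3. No main effect, time counted from baseline.** Given baseline, the 3- and 6-month scores each have variance 1.1025(1 − ρ²) and covariance 1.1025 × ρ(1 − ρ). Call this matrix Σ and let c = (3, 6). The slope difference has variance (2/80)/(c′Σ⁻¹c). Under a plateau d = (0.53, 0.53), the expected slope is c′Σ⁻¹d/(c′Σ⁻¹c), compared with 0.53/6 = 0.0883.

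| ρ | SE of slope | Power, linear growth | Same, design effect 1.3 | Expected slope under plateau | Overstatement |
|---|---|---|---|---|---|
| 0.1 | 0.0255 | 93% | 86% | 0.104 | 18% |
| 0.3 | 0.0254 | 94% | 86% | 0.100 | 13% |
| 0.5 | 0.0236 | 96% | 91% | 0.096 | 9% |
| 0.7 | 0.0197 | 99% | 98% | 0.093 | 5% |

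If errors within an employee are treated as independent, the plateau slope is (3 × 0.53 + 6 × 0.53)/(9 + 36) = 0.106, which is 20% too large.

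**4. Baseline-adjusted difference at 6 months.** SE = 1.05 × √(2(1 − ρ²)/80). Power for 0.53 is 89%, 92%, 96% and 99% at ρ = 0.1, 0.3, 0.5 and 0.7, or 80%, 84%, 90% and 98% with the 1.3 design effect.

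**The case against.** The strongest reply is that the protocol lists only time and time-by-treatment. Read literally, with time from baseline, that is a recognised model with arms equal at month 0. It targets the stated slope and has ample power. This stands, and it rules out the stronger conclusion a reader might draw, that the plan cannot estimate its own quantity or would necessarily miss a real effect. It does not settle the point, because the text does not exclude a main effect or state the time origin, and most analysts would add the main effect by default.

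Second, under exact linearity the slope from month 3 to 6 equals the slope from month 0 to 6. That is true, so under the protocol's own assumption the failure with a main effect is one of power, not of target. The plateau is a plausible scenario, not one the document states.

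Third, with baseline as a covariate, change scores and raw scores give the same treatment coefficients. So the Employees section conflicts over which visits count more than over the form of the response.

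Fourth, fixed-effect lists and time coding may properly sit in an analysis plan not shown. But the article does fix the responses and the tested term, and it attaches 80% power to them.

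A reader might also infer even lower figures (19-31% power, 1-3% rejection under a plateau), since only OP random effects are named. Those need errors to be treated as independent within employee. The document does not state the residual covariance, and a valid test of a zero interaction rejects at about 5%.

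**Conclusion.** The point holds in conditional form. The plan states a baseline-anchored 6-month effect and sizes the trial in a way that matches one, but describes a test on months 3 and 6 that is anchored at baseline only if no treatment main effect is fitted and time starts at month 0. With a main effect, power is about 22-54% instead of 80%, and an effect complete by month 3 is detected only at about the false-positive rate. Without it, power is about 86-98% after a 1.3 design effect, with a plateau overstated by roughly 5-20% depending on the error structure. These figures rest on 80 analysed per arm, SD 1.05 at each visit and assumed exchangeable correlations of 0.1-0.7. Because the outcome of the primary test can turn on this choice, it should be settled before unblinded analysis.

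**What to change.** Delete the restriction to the 3- and 6-month scores. Use T1, T2 and T3 as responses, with an employee-level covariance in addition to the OP effects. State the fixed effects and the time origin, and name one baseline-anchored primary contrast, either:

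- the baseline-adjusted between-arm difference at 6 months, from a model with treatment, visit, treatment-by-visit and baseline satisfaction. This is consistent with the 80 per arm and has about 80-98% power with the 1.3 design effect, from the 6-month score alone; or
- the slope difference from month 0, with arm means constrained equal at baseline.

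Either is acceptable; demoting the slope is a choice and not a requirement. Align the Sample size calculation, Employees and Statistical analysis sections with the one chosen, in a dated change before unblinded analysis. The cost is analysis wording only, with no new data or participants. The small downside of the 6-month contrast is giving up the single slope as the headline; the slope option still relies on linearity.
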